#### Concealment mechanism {16b}

The randomization codes are accessible to all study sites in a shared trial list. The list is located in a secure “container” on the internet that can be accessed after registration (www.tresorit.de). Access is granted after two-factor authentication. No personal patient data are stored in the online directory. The list contains study ID, group affiliation, a unique dial-in pin for the alley application, the study arm (hip or knee), a selection field for marking the ID used, and a selection field for marking the hospital. The assignment of the allocated IDs to corresponding patients is handled by the participating hospital sites themselves. Therefore, the assignment list (code to patient) is only available to the treating hospital. At the time of recruitment, the treating physicians had no knowledge of which group the patients were assigned to.

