### Recruitment {15}

Recruitment is performed by medical consultants in each of the eight study locations. Immediately after surgery indication for total hip/knee arthroplasty (THA/TKA), patients will be informed about the study and receive further information material. The patients are addressed directly by the attending physician, which increases compliance to study participation. Each study site recruits both patients with knee or hip problems and allocate these patients to the corresponding group based on the randomization sequence.

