### Assignment of interventions: allocation

#### Sequence generation {16a}

A 1:1 randomization has been conducted, assigning patients to either CG or IG for THA or TKA, respectively. For this purpose, two randomization lists have been created using Excel random number generator, creating separate lists for THA and TKA. These lists contained a predefined identification code for each indication, which was randomly assigned to the IG or CG. If patients agreed to participate, they were assigned to this list and thus received a unique identification code. This personal code serves as login for the “alley” application. As the randomization list was a shared online document for all study sites, simultaneous double submissions had to be avoided. For this reason, block randomization has been used for blocks of 50 patients. This means that each of the eight study sites is allocated to a fixed slot of 50 patients on the randomization list. During patient recruitment, these slots are successively filled. If more than 50 patients are to be recruited, new slots can be released at the end of the list. The randomized allocation of patients to either IG or CG allows minimizing the inclusion of patients with strong affinity for using digital applications in the IG. Randomization will ensure an equal distribution of patients.

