#### Implementation {16c}

Physicians make use of the pre-randomized lists and allocate patients to the next unused slot, starting from the top. The assignment to either IG or CG is performed during consultation. After screening and handing out study information, the patient is directly allocated to IG or CG by the physician. For this purpose, the physician accesses the secure online “container,” selects the next free slot with an ID code in the randomization list, and assigns it to the patient. The extracted ID code must be entered in the alley application via installation and indicates to which group the patient has been assigned to. After this outpatient clinic appointment, patients have time to decide whether they want to participate till the next consultation (approx. 14 days before surgery). In the case of study participation, the group allocation remains; otherwise, the ID will be removed.

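### The protocol's claim that recruiting physicians did not know the group is contradicted by its own allocation mechanism: a shared list, opened by those physicians, that contains group affiliation, with no masking described

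*Protocol article*

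**What the plan says.** All references are to the protocol article.

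- **Sequence generation {16a}.** There are separate lists for hip and knee, with the group fixed beforehand: "These lists contained a predefined identification code for each indication, which was randomly assigned to the IG or CG". The list is one online document shared by the sites, and each of the eight sites has a fixed run of 50 places on it. The section puts the patient's agreement before entry on the list. It also relies on randomisation to limit the share of digitally inclined patients in the intervention group.
- **Concealment mechanism {16b}.** On access: "The randomization codes are accessible to all study sites in a shared trial list". On content: "The list contains study ID, group affiliation, a unique dial-in pin for the alley application". The list also has fields for hip or knee, for marking an ID as used, and for the hospital. Access needs two-factor login. The section then states: "At the time of recruitment, the treating physicians had no knowledge of which group the patients were assigned to".
- **Implementation {16c}.** Slots are taken in list order: "Physicians make use of the pre-randomized lists and allocate patients to the next unused slot, starting from the top". The physician opens the online container, "selects the next free slot with an ID code in the randomization list, and assigns it to the patient", and "the patient is directly allocated to IG or CG by the physician". The patient then has until the next consultation to decide, and the ID is removed if the answer is no.
- **Who will take informed consent? {26a}.** The patient already has a group when told about the study, and the allocation is cancelled on refusal.
- **Recruitment {15}.** The person who recruits is the treating doctor: "The patients are addressed directly by the attending physician, which increases compliance to study participation".

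**The concern.** Concealment means that whoever decides whether and when to approach a patient cannot know the arm that patient would get. Here the person who screens, approaches and allocates opens a file that is said to hold the arm of every ID, used or not. If that column can be read, the physician knows the next arm and the later ones in the site's run. A patient comfortable with apps could be approached when an intervention slot is next, or a frail patient when a control slot is next.

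The second route does not need foreknowledge of the list. The arm is drawn before the patient decides, the physician and patient can both know it while the decision is open, and a refusal removes the patient from the randomised set. Willingness to take part may differ between being offered the app's content and being offered questionnaires only.

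Concealment carries much of the weight in this trial. Patients and staff are unblinded (Who will be blinded {17a}), and the primary outcome, HOOS or KOOS change at 3 months, is patient-reported. The Strengths and limitations section attributes group differences in these scores directly to the intervention because the trial is randomised. That inference needs arms formed independently of prognosis and motivation.

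**Working it through.** The protocol gives no figure for this point, so the main check sets the sections side by side.

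**1. Could the recruiter know the next arm?**

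| Question | Answer in the protocol article | Section |
|---|---|---|
| When is the group attached to the ID? | In advance | {16a} |
| Is the group on the list? | Yes | {16b} |
| Who can open the list? | All sites | {16b} |
| Who opens it to allocate? | The recruiting physician, in the consultation | {16c} |
| Is masking, locking or third-party release described? | No | {16a} to {16c} |
| Did physicians know the group at recruitment? | Said not to | {16b} |

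The first five answers do not lead to the sixth. Two-factor login keeps outsiders out, but the recruiters are authorised users. Using slots from the top fixes which slot comes next; it does not fix which patient is approached, or when.

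**2. Order of consent and allocation.** {16a} has agreement first and entry on the list second. {26a} and {16c} have allocation first, decision second, and cancellation on refusal. Both cannot describe the same procedure.

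**3. How foreseeable is the next arm?** If the column is readable, it is known with certainty. If it is hidden and a run of 50 is balanced 25:25 (an assumption; the protocol states 1:1 and 50), the best guess from past allocations was right 57.9% of the time in 20,000 simulated runs, against 50% by chance. Visibility of the column is therefore what matters; the length of the run is minor.

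**4. What a given bias would do (illustration only).**

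Inputs: SD of the change score 15 and 100 per arm, both from Sample size {14}; two-sided 5% test, critical value 1.96; no true effect. The bias in points is assumed. One way to reach 1.5 points: 15% of intervention slots go to patients who would improve 5 points more than average, and 15% of control slots to patients who would improve 5 points less, so 0.15 × 5 + 0.15 × 5 = 1.5. No section supports these shares or shifts.

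- SE of the difference = 15 × √(2/100) = 2.12
- Shift = bias / SE
- Type I error = Φ(−1.96 + shift) + Φ(−1.96 − shift)

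| Assumed bias | Shift | Two terms | Type I error |
|---|---|---|---|
| 0.5 | 0.236 | 0.0423 + 0.0141 | 5.6% |
| 1.5 | 0.707 | 0.1051 + 0.0038 | 10.9% |
| 3.0 | 1.414 | 0.2926 + 0.0004 | 29.3% |

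With the 61 per arm that the protocol needs for analysis, SE = 15 × √(2/61) = 2.72, and the same three biases give 5.4%, 8.6% and 19.7%.

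**The case against.** The strongest reply is that the protocol never says the recruiter can see the group column. It says the list contains the group, and it says outright that physicians did not know it. {16c} adds that the ID typed into the app shows which group the patient is in, which fits an arm revealed through the app. This stands: visibility is inferred. A reader might conclude that allocation was in fact unconcealed, and the text does not establish that. It does establish that the section written to explain concealment describes a mechanism that does not deliver it, and names no step that would.

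A second reply is that the time of recruitment may mean the approach to the patient, before the list is opened. That covers a physician's first use at best. Each later approach comes after earlier openings of the same list.

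A third reply is that slots must be taken in order, that every participant must own a device, and that controls install the app too. These narrow the room for selection. A physician who follows the order cannot choose an arm for a given patient, and patients without a device are excluded from both arms. The choice of whom to approach, and when, remains. The planned baseline comparison with adjustment cannot address unmeasured differences such as motivation.

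Finally, the type I error figures rest on assumed biases. That is correct. It would be wrong to read about 11% as an estimate for this trial; the answer moves from about 5.6% to 29% across biases that the documents can neither confirm nor exclude.

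**Conclusion.** The point holds as a contradiction in the protocol. The statement that physicians did not know the group is not supported by the list's described content, access and use, and as described the coming allocations in a site's run of 50 appear foreseeable. The conflict over whether consent precedes allocation is separate and certain; on the version in {26a} and {16c}, it adds a route to selection by arm even if the column was hidden.

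Whether selection occurred, and how large any bias is, cannot be determined from the document. The illustrative range is about 5.6% to 29% for an assumed bias of 0.5 to 3 points at SD 15 and 100 per arm, somewhat less at 61 per arm. The point should be settled before the primary result is interpreted, because an open-label comparison of patient-reported scores depends on concealed allocation.

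**What to change.** **If patients are still being allocated:**
- Keep group affiliation off any list the sites can open, and also the PINs of unused IDs. The ID or PIN gives entry to the app, so an unused one could be tried to discover its arm even with the column hidden.
- Release one ID at a time, and reveal the arm only after participation is agreed and the ID is recorded as used. The app already links ID to group.
- Reconcile {26a}, {16a} and {16c} so that one order of consent and allocation is stated.

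**If recruitment has already run**, which is likely because Trial status has it starting in 2021 and ending in early 2022:
- State how the group column was hidden from recruiting physicians. If it was not hidden, withdraw the concealment statement and report that the list was visible.
- Report the number who declined after allocation, by arm and separately for hip and knee.
- Compare the order in which IDs were used, and baseline characteristics by arm, within each site. This can reveal selection but cannot rule it out.

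**Cost.** The change before or during recruitment is small, but it is more than hiding one column: it alters the list, how IDs are released, and the consent sequence, since the patient would decide before learning the arm. After recruitment, the cost is a clarification and a few descriptive tables, provided that cancelled allocations and order of use were recorded.

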#### Implementation {16c}

Physicians make use of the pre-randomized lists and allocate patients to the next unused slot, starting from the top. The assignment to either IG or CG is performed during consultation. After screening and handing out study information, the patient is directly allocated to IG or CG by the physician. For this purpose, the physician accesses the secure online “container,” selects the next free slot with an ID code in the randomization list, and assigns it to the patient. The extracted ID code must be entered in the alley application via installation and indicates to which group the patient has been assigned to. After this outpatient clinic appointment, patients have time to decide whether they want to participate till the next consultation (approx. 14 days before surgery). In the case of study participation, the group allocation remains; otherwise, the ID will be removed.

### Assignment of interventions: blinding

#### Who will be blinded {17a}

Neither patients nor medical stuff are blind to the intervention. Patients know whether they are IG or CG by receiving educational content or just receiving questionnaires by the app. Medical stuff will receive information on patients` medical history only from patients of the IG. Therefore, blinding during the study is not possible. However, statistical analysis is performed by a blinded analyst.

#### Procedure for unblinding if needed {17b}

Not applicable. No unblinding necessary, as trial participants and care providers are not blinded. Unblinding of the data analyst is not intended.

### Data collection and management

#### Plans for assessment and collection of outcomes {18a}

The collection of patient data is exclusively performed in digital form through the alley application. Both standardized and self-constructed questionnaires are used (Table 2). All data are registered pseudonymously in an online database.

#### Primary outcome: physical functioning

To measure the global physical functioning of the hip, the widely utilized 40-item-version of the Hip Osteoarthritis Outcome Score (HOOS) will be used. The score evaluates patient outcomes in the five subscales pain, symptoms, activity of daily living, sport and recreation function, and hip-related quality of life. The HOOS includes all Western Ontario and McMaster Universities Osteoarthritis Index (WOMAC LK 3.0) questions. The score demonstrates good construct validity and high responsiveness [22]. Physical functioning of the knee will be measured with the Knee injury and Osteoarthritis Outcome Score (KOOS). The score measures physical functioning on the same subscales and has a sufficient test-retest reliability and convergent as well as divergent construct validity [23, 35].

#### Pain

A unidimensional single-item visual analog scale (VAS-pain) is used to measure pain intensity within the last week. Pain values were measured by placing a mark on a 10 cm line representing a range between “no pain” and “worst pain.”

#### Depression and anxiety

The 21-item depression, anxiety and stress scale (DASS) is applied to screen signs of depression and anxiety. The instrument has three subscales: depression, anxiety, and stress, each with seven items. The reliability by means of Cronbach’s alpha ranged from .76 for the subscale anxiety to .88 for depression. Sensitivity (77%) and specificity (83%) are good and achieve similar results compared to established test questionnaires, e.g., Hospital Anxiety and Depression Scale [24].

#### Physiological, mental, and social health

The Patient Reported Outcomes Measurement Information System (PROMIS-29) is a research initiative to improve and standardize the measurement of self-reported physical, mental, and social health characteristics. The 29-item score surveys seven health domains (physical function, fatigue, pain interference, depressive symptoms, anxiety, ability to participate in social roles and activities, and sleep disturbance) and in addition pain in a numeric rating item ranging from 0 to 10 (no pain to worst pain). The items of the PROMIS-29 are combined into a physical and a mental health summary score with corresponding excellent reliability (.98 to .97) and good reliability [25].

#### Patient expectations

The 6-item credibility/expectancy questionnaire evaluates treatment expectancy and rationale credibility of patients. The expectancy factor of the questionnaire can predict outcome on some measures. In total, the score has a good of Cronbach’s alpha reliability of .85 [26].

#### Patient satisfaction

Patients’ Experience Questionnaire (PEQ) is a 16-item questionnaire on hospital stay. The questionnaire assesses satisfaction with physicians, nursing staff, and service. The reliability by means of Cronbach’s alpha can be considered very good ranging from .81 for service evaluation to .94 for nursing staff evaluation. Due to the good to very good correlation with scales from the Cologne patient questionnaire, the PEQ provides an initial good external validity [27].

#### Dispositional optimism and pessimism

The 10-item Life-Orientation-Test (LOT-R) survey individual differences between optimism and pessimism based on specific personality traits. The relevance of the construct of optimism has been impressively demonstrated in numerous studies. Longitudinal studies have shown positive correlations with psychological well-being, physical health, health behavior, positive recovery processes, and lower mortality. The score shows moderate reliability of .69 for optimism and.59 for pessimism by means of Cronbach’s alpha [28].

#### Other outcomes

The other parameters risk of falling, post-operative complications, knowledge about the disease and postoperative behavior (patients’ health literacy), and perceived knowledge of the patient about the disease (physician questionnaire) are evaluated with self-constructed questionnaires. The knowledge questions for the patient represents the topics of the information provided by the alley application.

### Plans to promote participant retention and complete follow-up {18b}

The electronic data collection enables time and cost reductions, as well as compliance with quality standards through automatic completion checks. Patients are reminded to fill in the questionnaires by the app. In addition, each patient receives 150 EUR after the questionnaire completion 3 months after surgery. Due to the study design and the adjuvant design of the alley intervention, a deviation from intervention protocols is not expected. Further actions to ensure a complete follow-up at all measurement time points are not intended.

### Data management {19}

All data entries of the patients are made in the alley application and stored online. The data platform is hosted in a highly secure data center in Germany (Düsseldorf, RZ equinix. DU1). Only pseudonymized data is stored with the patient’s consent. The complete study data can only be viewed by the study primary investigator (JH) for the purpose of data analysis. The electronic data collection enables automatic checks for completeness and plausibility. Input errors can be excluded due to the study design.

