#### Interim analyses {21b}

After 3-month post-surgery, the main analysis will be performed to address the primary research question. The analysis will be conducted by a blinded statistician and the results will be published. Main analysis will be conducted after twelve months by the same blinded statistician.

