#### Composition of the data monitoring committee, its role and reporting structure {21a}

Due to the direct input of data and the central digital storage with direct access by the primary investigator, a data monitoring committee is not necessary. There will be no external data and safety monitoring board. Data and safety monitoring will be the responsibility of the principal and associate investigators.

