## Data Availability

The study data are not available to the public. Study data can only be viewed and retrieved by the study primary investigator (JH).

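### The protocol claims a blinded analyst, but its data-access rules either shut that analyst out or leave the analysis to a primary investigator whom nothing keeps blind

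*Protocol article*

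**What the plan says.** All references are to the protocol article.

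**On blinding.** Who will be blinded {17a} says that patients and staff know the arm, but that "statistical analysis is performed by a blinded analyst". Procedure for unblinding {17b} adds: "Unblinding of the data analyst is not intended". Interim analyses {21b} says of the 3-month comparison: "The analysis will be conducted by a blinded statistician and the results will be published". It then says: "Main analysis will be conducted after twelve months by the same blinded statistician".

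**On access.** Data management {19} states: "The complete study data can only be viewed by the study primary investigator", and names analysis as the purpose. Data Availability states: "Study data can only be viewed and retrieved by the study primary investigator". The section on the data monitoring committee {21a} cites "direct access by the primary investigator" to the central storage as one reason why no committee is needed, and makes the principal and associate investigators responsible for data and safety monitoring.

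**On the link between ID and arm.** Concealment mechanism {16b} describes a shared online list, open to all study sites, that shows the group next to each study ID. Implementation {16c} says that the ID entered in the app identifies the patient's group.

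**The concern.** Patients know their arm, and the primary outcome (HOOS or KOOS) is a questionnaire that they fill in themselves. Blinding of the analyst is therefore the only blinding the trial claims. The article describes no other independent check: there is no steering committee {5d}, no data monitoring committee {21a} and no structured audit after site training {23}.

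Blinding the analyst matters most where the analysis depends on the data, and Statistical methods {20a} leaves two such decisions open. The choice between the t-test and the Mann-Whitney test rests on a Kolmogorov-Smirnov test together with histograms and QQ-plots, with no rule for the case where they disagree. Risk adjustment is applied if baseline differences are seen, with no stated threshold. An analyst who knows the arms could let either decision follow the result, even without intending to.

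**Working it through.** No arithmetic underlies the point. It is a check of whether the statements on blinding and on access can both be followed as written.

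1. **What blinding requires.** Someone must analyse the outcomes by group without knowing which group is which ({17a}, {17b}, {21b}).
2. **What access allows.** One person may view the complete data, for analysis {19}, and one person may view and retrieve them (Data Availability). Both sections name the primary investigator, and both use the word only.
3. **Case A: the statistician is a different person.** Sections {19} and Data Availability then do not permit that person to view or retrieve the data. The analysis promised in {21b} cannot be done under the stated rules.
4. **Case B: the primary investigator is the analyst.** That person has the complete data and direct access to the storage and, taken as one of the investigators named in {21a}, also monitors the trial. Pseudonymous IDs do not mask the arm, because {16b} and {16c} tie each ID to a group. Nothing in the text keeps this analyst from making the link.
5. **Is there a third arrangement in the text?** No section describes a masked extract, recoded group labels, or a hand-over from the investigator to a separate statistician.
6. **What is exposed.** Two data-dependent decisions (test, adjustment) in each of two separately analysed indications: 2 × 2 = 4 decision points around the primary comparison.

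A subsidiary point lies in {21b}. The 3-month results are to be published, and the same statistician is still called blinded at twelve months. The article does not say how blinding survives that publication.

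**The case against.** The strongest reply is that the access sentences describe control of the database, not preparation of the analysis file. The word only cannot be wholly literal, because physicians may see intervention patients' data on the dashboard ({11a}, {17a}). The investigator could export a coded file to an independent statistician, and a full protocol or SAP might say so. Details such as who holds the key are commonly left to those documents.

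That arrangement is possible and would resolve the conflict. But the article is not merely silent: it states exclusive access twice, once with analysis as the purpose, against a blinding claim made in three sections. That is a conflict within the current text, not a missing detail.

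Several stronger readings are tempting and do not hold:

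- **The primary investigator has access throughout the trial.** Section {21a} speaks of direct access and a monitoring role but gives no time span.
- **The primary investigator knows the allocation.** The article never says so. It only fails to prevent it.
- **Anyone with IDs and outcomes is unblinded.** That person would also need the allocation list. The sites have the list, but under {19} they do not have the complete outcome data, and nothing says that the statistician is given the list.
- **The per-protocol set is a third exposed choice.** Section {20c} bases the main analyses on intention to treat alone and uses the per-protocol analysis only to validate them, so it is not a material exposure.

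It is also fair to say that the primary endpoint, time point and default test are fixed, that both decisions have a stated trigger, and that the main route to bias, self-report by patients who know their arm, remains whatever is done here.

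**Conclusion.** The point holds as a conflict between sections: the analyst blinding is stated, and the access rules as written do not support it. This does not show that the analysis will be unblinded or that the primary investigator will be the analyst.

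The size cannot be quantified from the article. The exposure is confined to the choice of test and the decision to adjust, in each indication. The conclusion assumes that the word only in {19} and Data Availability means what it says about the complete study data, and that no document outside the article already provides a masked hand-over. If one does, the article's wording still needs to be aligned with it.

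This should be corrected, because a stated safeguard against bias is involved and the remedy is cheap. A/B coding has a limit: it hides which arm is favoured, but not the size of the difference.

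**What to change.** Amend Data management {19} and Data Availability so that the blinded statistician of {21b} receives an extract in which study IDs are replaced and the arms are recoded A/B within each indication. The key should be held by someone other than the statistician and released only after the 3-month primary analysis is locked. The statistician should have no access to the shared allocation list.

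The primary investigator keeps the access needed for monitoring under {21a} but does not make the analysis choices. Restricting that person to pooled reports would collide with the monitoring role and is not needed. Section {21b} should say whether, and how, blinding is still claimed at twelve months.

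If the primary investigator is in fact to do the analysis, delete the blinding claim in {17a}, {17b} and {21b}.

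The cost is a change of access rights, one recoded extract, a named key holder and some wording. The statistician is already foreseen, and sample size, outcomes and patient burden do not change.
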